# ^11^C-methionine in the diagnostics and management of glioblastoma patients with rapid early progression: nonrandomized, open label, prospective clinical trial (GlioMET)

**DOI:** 10.1186/s12885-024-12469-2

**Published:** 2024-06-15

**Keywords:** Glioblastoma, Rapid early progression, Radiopharmaceutical, ^11^C-methionine, Clinical trial, Positron emission tomography, Radiotherapy

## Abstract

**Background:**

Glioblastoma (GBM) is the most common and aggressive primary brain cancer. The treatment of GBM consists of a combination of surgery and subsequent oncological therapy, i.e., radiotherapy, chemotherapy, or their combination. If postoperative oncological therapy involves irradiation, magnetic resonance imaging (MRI) is used for radiotherapy treatment planning. Unfortunately, in some cases, a very early worsening (progression) or return (recurrence) of the disease is observed several weeks after the surgery and is called rapid early progression (REP). Radiotherapy planning is currently based on MRI for target volumes definitions in many radiotherapy facilities. However, patients with REP may benefit from targeting radiotherapy with other imaging modalities. The purpose of the presented clinical trial is to evaluate the utility of ^11^C-methionine in optimizing radiotherapy for glioblastoma patients with REP.

**Methods:**

This study is a nonrandomized, open-label, parallel-setting, prospective, monocentric clinical trial. The main aim of this study was to refine the diagnosis in patients with GBM with REP and to optimize subsequent radiotherapy planning.

Glioblastoma patients who develop REP within approximately 6 weeks after surgery will undergo ^11^C-methionine positron emission tomography (PET/CT) examinations. Target volumes for radiotherapy are defined using both standard planning T1-weighted contrast-enhanced MRI and PET/CT. The primary outcome is progression-free survival defined using RANO criteria and compared to a historical cohort with REP treated without PET/CT optimization of radiotherapy.

**Discussion:**

PET is one of the most modern methods of molecular imaging. ^11^C-Methionine is an example of a radiolabelled (carbon 11) amino acid commonly used in the diagnosis of brain tumors and in the evaluation of response to treatment. Optimized radiotherapy may also have the potential to cover those regions with a high risk of subsequent progression, which would not be identified using standard-of-care MRI for radiotherapy planning. This is one of the first study focused on radiotherapy optimization for subgroup of patinets with REP.

**Trial Registration:**

NCT05608395, registered on 8.11.2022 in clinicaltrials.gov; EudraCT Number: 2020–000640-64, registered on 26.5.2020 in clinicaltrialsregister.eu. Protocol ID: MOU-2020–01, version 3.2, date 18.09.2020.

## Introduction

### Background and rationale {6a}

Compared to other oncological diagnoses, primary brain tumours are less common, with an incidence of 8/100,000 population. Unfortunately, the most aggressive tumors, glioblastomas (GBM), account for approximately half of all primary malignant brain tumors in adults. Due to their biological behaviour, these tumours are ranked among the most difficult-to-treat diseases and therefore represent a serious health problem despite the relatively low incidence. Despite advances in the complex oncological treatment of gliomas, treatment results remain unsatisfactory [1, 2].

The reported median survival of 14–17 months with a five-year survival of 10% is observed mainly in patients with favourable prognostic factors who undergo complete adjuvant oncological therapy [3, 4]. Despite all efforts, the median overall survival has only increased by a few months over the past thirty years. For this reason, further research and development of new therapeutic procedures are necessary with the aim of ensuring better disease control and prolonging overall survival [5].

Clinical studies evaluating the role of modern targeted therapy and immunotherapy have not yet demonstrated higher effectiveness of this treatment strategy, and the results of GBM treatment have thus not fundamentally changed. The only small advance in the last 15 years has been treatment using alternating electric fields emitted from electrodes taped to the scalp (Optune). However, the broader availability of this method is limited by the enormously high cost, patient motivation, and some debatable issues in the clinical trials performed [6, 7].

The current standard of care for GBM is based on a multimodal approach combining the maximum possible and safe surgery, postoperative radiotherapy (RT), and chemotherapy (CHT) with alkylating cytostatic temozolomide (TMZ). Adjuvant therapy is usually started within 4 to 6 weeks after surgery, during which the patient recovers from surgery, and all necessary procedures (multidisciplinary indication committee, preparation of radiation plan, etc.) take place before further oncological treatment. The standard postoperative management of newly diagnosed patients with GBM has remained unchanged since the published results of the EORTC 26981–22981/NCIC CE3 trial (Stupp regimen), which completed patient recruitment as early as 2002 and published the findings in 2005. In this protocol, TMZ (75 mg/m^2^) is administered on days 1 to 42 concurrently with RT (60 Gy), followed by TMZ alone (150 to 200 mg/m^2^) on days 1–5 in six consecutive 4-week cycles. Coadministration of RT and TMZ improved survival from 12.1 months (with RT alone) to 14.6 months (with the addition of TMZ) (3). Due to a certain stagnation in the treatment of GBM in recent years, intensive research at all levels is necessary to improve patients' perspectives on this unfavourable diagnosis.

The Perry accelerated regimen [8] is a treatment option for patients aged ≥ 65 years and those for whom long conventional RT (60 Gy in six weeks) combined with chemotherapy is considered unsuitable by their treating physicians. The total RT dose for this accelerated regimen is 40.05 Gy, administered in 15-day fractions over three weeks.

Concomitant TMZ is administered here at a dose of 75 mg/m^2^ per day for 21 consecutive days from the start of RT until its termination. As with Stupp's regimen, adjuvant TMZ alone follows at 150 to 200 mg/m^2^ daily for five consecutive days of a 28-day cycle, up to 12 cycles or until disease progression. For patients who are not candidates for concomitant chemoradiotherapy (regardless of age), individual adjuvant treatment is indicated as standard, usually accelerated RT alone (total dose 30–50 Gy in a 10–20-day dose, for example, fractionation regimens of 10 × 3.0 Gy, 10 × 3.4 Gy, 15 × 2.67 Gy, 20 × 2.5 Gy and others), followed in some patients by TMZ palliative chemotherapy based on the actual overall condition of the patient.

#### Glioblastoma as a progressive disease

In connection with the greater availability of magnetic resonance (MR), it is possible to optimize the planning of radiotherapy according to the findings of the so-called planning MR for an increasing number of patients. It is an MR study performed immediately (approximately a few days) before the start of radiotherapy. Following the performance of this MR study (typically approx. 4–5 weeks after surgery), a new phenomenon called very rapid progression (REP, rapid early progression) is described. The REP diagnosis is based on comparing early postoperative MR findings (usually within 48–72 h after surgery) and planning MR before radiotherapy (preRT).

Retrospectively comparing early postoperative MR with preRT MR performed approximately 30 days later, Farace et al. described 30% of preRT MR with signs strongly suggestive of tumour progression during this period [9]. An even more significant proportion of patients with documented REP was described by Palmer et al., where up to 52% progressed before starting adjuvant therapy without any effect of waiting time to start RT (median time from resection to RT was 32.5 vs. 33 days in patients with REP vs. without REP (*p* = 0.337) [10]. These results are consistent with our retrospective analysis of 90 patients with GBM treated between 2014 and 2017, where 51% of patients had suspected REP at planning preRT MR [11]. These patients represent a subset with particularly aggressive GBM requiring further intensive research and possibly treatment modification.

According to these and several other retrospective analyses, it was confirmed that the presence of early progression on planning MR was associated with a more aggressive form of GBM and worse overall survival [12–14]. A higher risk can, of course, be expected in patients after nonradical resections [14]. It is still unclear what further influences the prognosis of patients with early progression. Palmer et al. even described significantly worse survival in patients with unmethylated MGMT (O6-methylguanine-DNA methyl-transferase), the methylation of MGMT is considered a marker of higher chemosensitivity [10]. Analysis of other potential biomarkers still needs to be improved. Due to a large number of patients with REP and the retrospective nature of the studies carried out thus far, it is essential to analyse this more aggressive subgroup of tumors prospectively and try to influence the negative course of the disease more clinically.

The optimal treatment approach for patients with REP needs to be determined. It is unclear whether it is better to indicate repeat surgery for recurrence, choose accelerated RT regimens with or without concurrent chemotherapy, or directly administer more aggressive and intensive chemotherapy with a combination of alkylating cytostatics if MGMT methylation is present [15]. Treatment of these patients with REP currently does not differ from that of patients without REP; if so, it is a purely individual approach. These patients distorted the results of previous clinical trials where routine MR examination was not performed before RT. Currently, these patients are usually excluded from clinical trials.

Moreover, current clinical trials often randomize patients until after concomitant chemoradiotherapy if there is no progression on follow-up MR after chemoradiotherapy. REP on planning MR is a significant negative prognostic factor that should be a stratification factor in future clinical trials. In general, the aggressive character of GBM is manifested by its microenvironment, the molecular background of glioma cells, or the miRNA profile, which may be essential in GBM oncogenic signalling and has the potential to serve as a biomarker of this disease and a new therapeutic target in oncology [16–22].

#### Radiotherapy in the treatment of glioblastoma

Due to the almost zero risk of developing distant metastases, and on the contrary, due to the nearly 100% risk of developing local recurrence in the brain, in the case of GBM, great emphasis is placed on local treatment methods, i.e., surgery and radiation. Radiotherapy has experienced a stormy development in the last decade due to improved computer technology, greater availability of imaging methods, and more advanced radiotherapy systems [7, 23, 24]. A crucial part of radiotherapy treatment is correctly determining the target area for the prescribed radiation dose. In the case of brain tumours, the gold standard for defining target volumes is MR imaging. Recently, the importance of additional imaging methods, especially PET imaging, for the closer characterization of gliomas has been emphasized [24, 25].

#### ^11^C-Methionine PET in the imaging of glioblastoma

Positron emission tomography is currently the most dynamically developing area for functional brain imaging. It is used both pretreatment and as part of the follow-up of GBM patients after treatment. The development of PET diagnostics is aimed not only at constructing more sensitive and robust PET scanners but also at introducing new radiopharmaceuticals, especially in centres with their own cyclotron.

Fluorodeoxyglucose (2-deoxy-2-[18F]fluoro-D-glucose, FDG) is the most commonly used radiopharmaceutical in PET/CT diagnostics in general. However, it may not provide optimal results for brain examination mainly due to the high metabolic activity in the physiological brain tissue, the image background. That is why other radiopharmaceuticals are used in the targeted diagnosis of brain tumors, most often different amino acid derivatives. Of these, [18F]-O-(2-fluoroethyl)-L-tyrosine (fluoroethyltyrosine, FET) and L-(S-methyl-[^11^C])-methionine (methionine, MET) play the most important roles. Carbon ^11^-labelled methionine is historically the most frequently used drug for glioma imaging.

Amino acid (AA) tracers, including FET and MET, naturally cross the blood–brain barrier through neutral amino acid transport mechanisms. Unlike naturally occurring methionine, the artificially prepared amino acid FET is not subsequently incorporated into protein fractions [26, 27]. Their transport and incorporation into proteins are increased in tumour tissue. However, it is still being determined which of these mechanisms is more critical for PET imaging. Methionine is also incorporated into fats and nucleic acids; this incorporation is less significant for imaging brain tumours. Studies have confirmed the correlation between the intensity of MET accumulation, tumour grading according to WHO and proliferative activity assessed by the Ki-67 index [28] and the density of microvascularization [29]. Methionine is incorporated to an increased extent even in low-grade gliomas [30], while its accumulation is low in the background of normal brain tissue. Since the transport of AA tracers does not depend on the blood‒brain barrier violation, the accumulation of AA tracers can be detected even in tumours that do not show contrast saturation and enhancement during MR examination.

MET PET is more suited than MR to accurately delineate the target volume for radiotherapy and determine the extent of viable tumours. Conversely, MR shows the overall extent, including pathological changes associated with the tumour, such as oedema in the immediate vicinity. The widespread use of MET PET is most hindered by its short half-life, so the use of MET is limited only to centres with their cyclotron and the possibility of its production. In patients with REP glioblastoma, it is necessary to start oncological treatment as quickly as possible. It is, therefore, unethical to wait for the delivery of other commercially available radiopharmaceuticals labelled with fluorine 18 (18F-FET, 18F-FLT, 18F-DOPA, etc.), which have a longer half-life. They are also available in PET centres without a cyclotron, but only on predetermined and planned production days. In complex neuro-oncology centres, the possibility of individual preparation of MET is thus an opportunity to benefit patients with REP, the extraordinarily aggressive glioblastomas.

In addition to the subjective assessment, the evaluation of the PET image is refined by quantitative measurement. For this quantitative measurement in clinical practice, drawing a suitable area of interest and software evaluation of the SUVmax parameter ("maximum standardized intensity of accumulation") are usually used. The assessment of the SUVavg ("average value of the standardized intensity of accumulation") is chosen less often. Nevertheless, it is influenced by the specific location of the area of interest, with more significant variability between evaluators. Therefore, SUVavg is less suitable for standardized assessment in studies.

The area of interest can be either circular in the plane for one selected slice, 2D-ROI, or spherical in space, 3D—VOI. The two-dimensional region of interest is also very strongly influenced by the choice of a particular slice for assessment and is also burdened by low reproducibility and high interrater variability. For our evaluation, the measurement of SUVmax in a spatial 3D-VOI defined with a size of 1.5 cm was chosen to minimize variability.

The ratio of the radiopharmaceutical accumulation in the tumour relative to the background ("tumour-to-background" ratio, T/B) is used to differentiate the areas of the physiological and pathological intensity of accumulation. There is no definite recommendation on how to choose the background, and even any recommendations may be influenced by the possibilities of a specific patient. There are also no exact values of the T/B ratio defined as a threshold for distinguishing tumour tissue from physiological tissue. According to available literature data, values between 1.3 and 1.7 are usually chosen.

### Explanation for choice of comparator {6b}

This study is an open-label prospective clinical trial. The experimental drug ^11^C-methionine PET/CT will be administered to all patients recruited to this study and compared to the cohort consisting of a historical group of GBM patients with REP collected in the period 2014–2018.

### Objectives {7}

Patients diagnosed with GBM who develop REP before starting adjuvant radiotherapy have an abysmal prognosis. The optimal treatment for these patients has yet to be discovered, and no prospective clinical evaluation has been performed. We assume that the lesion detected on MR is not the only area of REP development. It may be MET PET that can reveal other areas of the aggressive part of the tumour, and the subsequent RT can then be better planned to increase the time to progression in such a cohort of patients. Therefore, the purpose of this study was to refine the diagnosis in patients with GBM with proven REP and subsequent optimized planning of the following treatment procedure. Chemotherapy will be administered as standard treatment to all patients.

### Trial design {8}

The GlioMET study is an investigator-initiated study. This clinical trial is a prospective, monocentric, open-label, nonrandomized clinical study with a parallel assignment initiated in June 2020.

The main aim of the clinical trial is to improve the progression-free survival of patients with GBM and REP via optimizing of diagnostic and treatment procedures. The experimental drug ^11^C-methionine PET/CT will be administered to all patients recruited to this study and compared to the cohort consisting of a historical group of patients collected in the period 2014–2018. The setting is a confirmatory framework against the historical cohort. A schematic overview of the design of the study is presented in Fig. 1.

**Fig. 1 Fig1:**
[figure not shown]
The Schematic overview of the GlioMET study design. A_hist_ Arm – a historical arm. C-MET—carbon radiolabelled methionine. CT – computer tomography. GBM—glioblastoma multiforme. MRI – magnetic resonance imaging. PET/CT—positron emission tomography/computer tomography. PFS – progression-free survival. PS – performance status. REP—rapid early progression

## Methods: participants, interventions, and outcomes

### Study setting {9}

The GlioMET study is a monocentric study. The recruitment period began in October 2020. Patient recruitment in the Czech Republic is planned to be completed in February 2024.

Masaryk Memorial Cancer Institute in the Czech Republic, the coordinating centre for the study, is responsible for educating and training research staff, tracking participants’ enrolment, mathematical analysis, monitoring, pharmacovigilance, data management, and reporting of the study. The control cohort consisted of a historical group of patients collected in the period 2014–2018. Data are collected only from the Czech Republic.

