### Sample size {14}

A historical retrospective cohort included 44 patients with REP who were indicated for adjuvant chemoradiotherapy (Arm Ahist). The median PFS in this cohort was 4.9 months. Assuming that the time distribution in the Experimental Arm follows a proportional hazard model, a significance level of 5%, and a power of 80%, 65 events are needed to detect a hazard ratio of 1.65 (i.e., median PFS in the Experimental Arm of 8 months). With an assumed recruitment of 38 months and a follow-up duration of six months, 67 patients are needed based on the historical cohort. With the expected screening failure rate of 5% and a dropout rate of 5%, approximately 75 patients with confirmed REP should be enrolled.

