### Recruitment {15}

Recruitment of the patients has been carried out since October 2020. During the first four years, all planned patients will be recruited. The patients were recruited only at Masaryk Memorial Cancer Institute in Brno, Czech Republic.

The patient will be informed about the study during the visit, during which initial eligibility for the study will be determined, and the research staff will explain the study protocol and design.

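### The historical control arm stops in 2018, at least 21 months before the October 2020 start, with no reason given; the nearest controls are unused, and 44 control events give about 71–73% power if the test is two-sided.

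*Protocol article*

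**What the plan says.** Sections {6b}, {8} and {9} of the protocol article all date the comparator to 2014–2018; {9} puts it as "The control cohort consisted of a historical group of patients collected in the period 2014–2018". The same section states "The recruitment period began in October 2020". Trial design {8} adds "The setting is a confirmatory framework against the historical cohort".

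Sample size {14} gives the size of the control arm: "A historical retrospective cohort included 44 patients with REP who were indicated for adjuvant chemoradiotherapy". Their median PFS was 4.9 months. From a 5% significance level (sidedness not stated), 80% power and a hazard ratio of 1.65 (median 8 months in the Experimental Arm), {14} derives 65 events and 67 patients, recruited over 38 months and followed for 6.

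The introduction mentions "our retrospective analysis of 90 patients with GBM treated between 2014 and 2017, where 51% of patients had suspected REP". Recruitment {15} says "The patients were recruited only at Masaryk Memorial Cancer Institute in Brno, Czech Republic"; the centre that supplied Ahist is not named in so many words.

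**The concern.** With no randomisation, the hazard ratio carries any change over time in MR practice, REP reading, radiotherapy planning or later care. Section {20b} says adjusted analyses are not planned, although {20a} mentions multivariable Cox models, so the plan has no clear device to absorb such drift. The controls least exposed to it are the REP patients treated just before the trial opened, and they are left out.

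The control arm is also the smaller side of the comparison and cannot grow beyond 44 events, so it limits the precision of the primary result. If {14} assumed an equal number of control events, the stated 80% power is not what the trial has.

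**Working it through.** **Length of the gap.** If Ahist runs to December 2018, January 2019 to September 2020 is 12 + 9 = 21 months. It is longer if collection ended earlier in 2018.

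**Reproducing the 65 events.** With z = 1.960 + 0.842 (two-sided 5%, 80% power) and 1:1 arms:
- Freedman, HR 1.65: (2.802)² × (2.65/0.65)² ≈ 131 in total, 65.5 per arm.
- Schoenfeld, HR 8/4.9 = 1.633: 4 × (2.802)² / (ln 1.633)² ≈ 131 in total, 65.5 per arm.
- Schoenfeld, HR 1.65: about 126 in total, 63 per arm.

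So 65 matches the requirement for each arm. As a two-arm total it would have to be 126–136 (two-sided) or 99–108 (one-sided); as a one-sample test against a fixed median it would be about 25–33.

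**Power with 44 controls.** Power = Φ( ln HR / √(1/d₁ + 1/d₀) − z_α ), with d₁ = 65 trial events and every control counted as an event. For d₀ = 44, √(1/65 + 1/44) = 0.195. At HR 1.65, 0.501/0.195 = 2.565 and Φ(2.565 − 1.960) = 0.727. At HR 1.633, 0.490/0.195 = 2.511 and Φ(2.511 − 1.960) = 0.709. The factor by which the HR is multiplied and divided to give its 95% CI is exp(1.96 × 0.195) = 1.47.

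**How many patients the gap might hold.** The document gives no count, so these are assumptions:
- Ahist rate: 44 over 60 months = 0.733 a month; × 21 ≈ 15, giving 59 controls.
- Suspected-REP rate, 2014–2017: 0.51 × 90 ≈ 46 over 48 months = 0.956 a month; × 21 ≈ 20, giving 64 controls. This counts suspected REP, not patients selected by the Ahist rule, so it is an upper figure.

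| Control events | Two-sided power, HR 1.633 / 1.65 | One-sided power, HR 1.633 / 1.65 | 95% CI factor |
|---|---|---|---|
| 44 | 0.71 / 0.73 | 0.81 / 0.82 | ×1.47 |
| 59 | 0.78 / 0.80 | 0.86 / 0.87 | ×1.42 |
| 64 | 0.80 / 0.81 | 0.87 / 0.89 | ×1.41 |

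In the other direction, 80% two-sided power with 44 control events needs about 108 (HR 1.65) to 127 (HR 1.633) trial events, more than 67 patients can yield.

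**Calendar distance.** Assume uniform accrual and count months from January 2014. Ahist (months 0–60) has its midpoint at 30. The trial (October 2020 to February 2024, months 81–122) has its midpoint at 101.5. The distance is 71.5 months. Gap patients (months 60–81) centre on 70.5.
- 15 added: control mean (44 × 30 + 15 × 70.5)/59 = 40.3; distance 61.2 months, a cut of 10.3/71.5 = 14%.
- 20 added: control mean (44 × 30 + 20 × 70.5)/64 = 42.7; distance 58.8 months, a cut of 12.7/71.5 = 18%.

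In the extended arm 44/59 = 75% or 44/64 = 69% of controls would still date from 2014–2018.

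**The case against.** The comparator is defined consistently across {6b}, {8}, {9} and {14}, so nothing contradicts itself. The abstract dates the protocol to 18.09.2020, and patients irradiated in mid-2020 could not have supplied mature PFS for the 4.9-month reference. Freezing a completed cohort to size the trial was reasonable, and the reason for the cut-off may stand in the full protocol, which is not shown. This holds for the sizing. It does not explain leaving the gap patients out of the final comparison: at a median PFS near 4.9 months they would be mature long before a 44-month study ends.

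Recruitment was planned to end in February 2024 and the article appeared in June 2024. Changing the primary comparator of an open-label trial at that stage invites selection by people who may know outcomes, and locking a list does not blind the judgement of who had REP. Leaving out gap patients planned with MET PET could also leave a selected remainder. These objections stand, and they are why the extension should be supporting only.

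Three stronger inferences are tempting and not supported:
- A reader might infer that the extension closes the calendar gap. Only the edge-to-edge gap closes; most of the mean distance stays, and the control is still not concurrent.
- A reader might infer that the trial is underpowered outright. Section {14} does not state sidedness, and at one-sided 5% the shortfall disappears.
- A reader might infer that 15 to 20 usable records lie waiting at the same centre. Ahist's centre is inferred from the single-centre design and the investigators' reference to their own retrospective series; the yield and the availability of postoperative MR, planning MR and PFS are stated nowhere.

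**Conclusion.** The concern holds in a limited form. At least 21 months of the nearest potential controls are unused in a confirmatory historical comparison, and the article gives no reason. On the two-sided 5% reading that reproduces 65 as events per arm, the design has about 71–73% power rather than 80%; on a one-sided reading it has about 81–82%. About 15 more controls, or up to about 20, would raise two-sided power to about 78–81%. The gain in calendar closeness is modest.

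The figures assume 65 trial events, an event in every control, uniform accrual, and gap yields taken from past rates. Fewer events on either side would lower the power. The documents do not show that the cut-off was chosen to favour a result, nor do they justify replacing the primary comparator now.

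**What to change.** - Keep the 2014–2018 cohort as the primary comparator.
- Add a prespecified supporting analysis that extends Ahist to every eligible REP patient whose radiotherapy was planned without MET PET, up to the day before the first trial patient, under the same selection and reading rules. Lock the list and its PFS before the trial-arm comparison. Report how many gap patients were left out and why.
- State in {6b} why the primary cohort ends in 2018.
- In {14}, state whether the 5% is one- or two-sided, say that 65 is the number for the Experimental Arm if that is what is meant, and restate the power for 44 controls.
- Submit the change as an amendment under {25}, which requires ethics committee and national drug agency review and a registry update.

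The cost is retrieval of charts and MR for perhaps 15 to 20 existing patients, plus the amendment review. No new enrolment is needed. If the records prove unobtainable, the changes to {6b} and {14} still stand.
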